### Objectives {7}

The primary objective of the trial is to determine the time to first unplanned re-hospitalization or death (composite endpoint) in patients with liver cirrhosis who discontinue long-term PPI therapy (intervention group) as compared to patients who continue PPI therapy (control group) over a period of 12 months (360 days). Secondary objectives include an assessment and comparison of the following endpoints in the two groups:
Time to death and mortality (overall and liver-related),Time to and rate of unplanned re-hospitalization,Overall infection rates and infections rates differentiated by the site of infection,Rate of acute hepatic decompensation and acute-on-chronic liver failure (ACLF),Rate and source of upper and lower gastrointestinal bleeding events.

Furthermore, the changes in the intestinal microbiota in both groups and their impact on the primary endpoint will be assessed. The potential pharmacoeconomic impact of PPI discontinuation in patients with liver cirrhosis will be studied, too.

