### Outcomes {12}

The primary composite endpoint is the time to unplanned re-hospitalizations or death during the trial period. However, expected re-hospitalization for mere paracentesis (without other complication of cirrhosis) during a period of 30 days after discharge is not regarded as an “unplanned re-hospitalization”. If the local investigator and the clinical trial management come to a conflicting assessment whether a re-hospitalization was “planned” or “unplanned”, a blinded endpoint committee (consisting of three independent hepatologists) will resolve this disagreement.

Secondary endpoints are described in Table 2. Importantly, patients who reach the primary endpoint “re-hospitalization” will continue all study procedures and will further receive the study medication. Therefore, secondary endpoints will be studied after a study participant has reached the primary endpoint. Patients who reach the safety endpoint (evidence-based re-therapy with PPI; see Table 2) are censored at the respective time-point.

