### Sample size {14}

The sample size is based on the composite primary endpoint time to death from any cause or time to unplanned re-hospitalization from any cause. Based on previous studies on mortality in cirrhosis patients who receive PPI [5, 6, 10, 32, 33] and an assumed 50% risk for re-hospitalization 3 months after discharge in decompensated cirrhotic patients [20, 30, 50], it is expected that the control group will have a probability of 65% to reach the primary endpoint after 6 months. The risk to reach the primary endpoint in the PPI withdrawal group is assumed to be 50% after 6 months, due to a reduction of mortality [4–6, 8, 10, 11] and a decreased risk for infectious complications [8–10, 12–16], which results in a lower risk for re-hospitalization [20]. This corresponds to a HR of 0.66 of the intervention group compared to the control group. The sample size calculation is performed on the assumed event rates of 50% in the intervention group (PPI withdrawal) and 65% for the control group after 6 months with a two-sided significance level α of 5% and a power of 80%, which requires a total number of 184 events to be observed. With a follow-up period of exactly 360 days per patient and an estimated 20% random loss to follow-up or non-compliance it can safely be assumed that a sufficient number of events will have been observed by the end of the trial if a total of 475 patients are available for analysis (based on the log-rank test; PASS 16.0.3). Therefore, 476 patients will be randomized.

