## Statistical methods

### Statistical methods for primary and secondary outcomes {20a}

The primary efficacy endpoint analysis will be performed according to the intention-to-treat (ITT) principle based on the full analysis set (FAS). The effects of continuation or discontinuation of PPI therapy with respect to the primary endpoint will be estimated and tested by Cox regression. The regression model will include treatment arm and categorized the severity of cirrhosis (MELD ≤ 13 vs. > 13) as fixed effects and the study centre as a random effect. As an estimated effect size, the hazard ratio (HR) between the two treatment arms will be given with the corresponding 95% confidence interval. The one-sided test of the superiority of discontinuation of PPI over the continuation of PPI at significance level 2.5% will be based on the corresponding asymptotic two-sided 95% confidence interval from the Cox regression model. The null hypothesis is rejected if the upper limit of the confidence interval is below 1.0. The analysis of the treatment effect with respect to the individual components of the composite endpoint and to secondary endpoints will be performed analogously with the (cause-specific) Cox model. Time to event outcomes will be visualized by Kaplan-Meier curves stratified by treatment group. Adverse event data will be summarized by the treatment group.

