### Methods for additional analysis (e.g. subgroup analyses) {20b}

The composite primary endpoint will additionally be analysed descriptively by applying a multi-state model with states of unplanned re-hospitalization and death. Both analyses of the composite primary endpoint will be repeated in the per-protocol (PP) set. Analyses of the primary and secondary endpoint in the following subgroups are planned: According to the Child-Pugh stage; according to the aetiology of cirrhosis; untreated or treated aetiology of cirrhosis (e.g. treated vs. untreated viral hepatitis); patients with a history of TIPS implantation. Further subgroups may be defined in ad-hoc analyses.

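### Repeat re-hospitalizations and repeat infections enter no stated treatment comparison, although the secondary objectives name rates and follow-up continues after the first event

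*Protocol article*

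**What the plan says.** Four places in the protocol article bear on this point.

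- **Objectives {7}.** The primary objective is the time to the first event of the composite. Among the secondary objectives are "Time to and rate of unplanned re-hospitalization" and "Overall infection rates and infections rates differentiated by the site of infection". For re-hospitalization, time and rate are named side by side as two targets.
- **Outcomes {12}.** Patients who are re-hospitalized "will continue all study procedures and will further receive the study medication", and "secondary endpoints will be studied after a study participant has reached the primary endpoint". Table 2 lists unplanned re-hospitalization and any infection among the secondary endpoints.
- **Statistical methods {20a}.** The primary endpoint is compared by Cox regression with treatment arm and MELD category as fixed effects and centre as a random effect. For the components, and then for the remaining endpoints, the method is: "to secondary endpoints will be performed analogously with the (cause-specific) Cox model". No other comparative method is named for them.
- **Additional analysis {20b}.** The composite is also to be "analysed descriptively by applying a multi-state model with states of unplanned re-hospitalization and death". Infections are not part of that model.

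**The concern.** A Cox model analogous to the primary one follows each patient to the first event of the given type and returns a hazard ratio. A second or third admission, or a second infection, does not alter it. Yet the objectives speak of rates, and the design keeps patients treated and observed after the first admission, so these later events will be recorded.

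If rate means events per patient-time, the stated method does not estimate it. Two arms can have similar times to first admission and differ in the total number of admissions, or the reverse. The trial could then report no formal comparison of total admissions or total infections, although the data would be in hand.

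**Working it through.** **1. The plan's own figure.** Sample size {14} assumes "event rates of 50% in the intervention group (PPI withdrawal) and 65% for the control group after 6 months". Under exponential times, HR = ln(0.50)/ln(0.35) = 0.660, as stated. Events needed at two-sided 5% and 80% power:

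- Schoenfeld: 4 × (1.960 + 0.842)² / (ln 0.660)² gives 183.
- Freedman: (1.960 + 0.842)² × [(1 + 0.660)/(1 − 0.660)]² gives 188.

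The stated 184 reproduces within 3%, so the planned rates can be used as the starting point.

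**2. Hazards per 360 days.**

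- Control: 2 × ln(1/0.35) = 2.10.
- Intervention: 2 × ln(1/0.50) = 1.39.

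**3. Simplest case.** Assume that all of the composite hazard is admission, that it is unchanged after the first event, and that there is no dropout. With 476 patients, 238 per arm:

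- First events: 238 × (1 − e^−2.10) + 238 × (1 − e^−1.39) = 238 × 0.8775 + 238 × 0.75 = 209 + 178.5 = about 387.
- All events: 238 × (2.10 + 1.39) = about 830.
- Later events: 830 − 387 = about 442 before rounding, a share of 442/830 = 53%.

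**4. Allowing for death, dropout and a changed later rate.** Let λ be the composite hazard and f the part of it that is death, so that λ_D = fλ and λ_H = (1 − f)λ. Let m be the admission rate after the first admission relative to before, δ the dropout hazard, and T = 360 days. The death hazard is taken as the same before and after an admission. Per patient:

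- first admissions = λ_H × [1 − e^−(λ+δ)T] / (λ+δ)
- later admissions = m × λ_H × { [1 − e^−(λ_D+δ)T] / (λ_D+δ) − [1 − e^−(λ+δ)T] / (λ+δ) }

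Where λ_D + δ = 0, the first term in the braces is T. The plan's 20% loss is entered as δ = −ln(0.80) = 0.223 per 360 days. The values of f and m are assumptions; the document gives neither.

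Share of all admissions that are not first admissions, without dropout / with 20% dropout:

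| Death share f | m = 0.25 | m = 1 | m = 2 |
|---|---|---|---|
| 0% | 22% / 21% | 53% / 52% | 70% / 68% |
| 10% | 19% / 18% | 49% / 48% | 66% / 64% |
| 20% | 17% / 16% | 44% / 43% | 61% / 60% |
| 30% | 14% / 13% | 40% / 38% | 57% / 55% |
| 40% | 12% / 11% | 35% / 33% | 51% / 50% |

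With unchanged recurrence and 10% to 40% of the hazard being death, the share runs from 49% (no dropout) down to 33% (20% dropout). Over the whole table it runs from 11% to 70%.

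**5. Limits.** The constant hazard is itself an approximation. Sample size {14} also assumes a 50% re-hospitalization risk at 3 months, which at a constant hazard would give 1 − 0.5² = 75% at 6 months, not the 65% assumed for the composite. For infections the document gives no rate, so no share can be computed.

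**The case against.** The strongest reply is that rate need not mean events per patient-time. Sample size {14} uses event rates for cumulative proportions, the abstract speaks of rates of mortality, which cannot recur, and the document nowhere mentions counts or total admissions. If rate means the proportion with an event, first-event analysis with Kaplan-Meier curves goes most of the way. This stands, and for that reason one cannot say that the rate objective goes unanswered. It does not settle the matter. The term is undefined, time and rate are listed as separate targets, and when death competes, a cause-specific hazard ratio is not itself a comparison of proportions.

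A reader might also infer that the follow-up after re-hospitalization is wasted. The documents do not support that. The Discussion explains that most deaths are expected after re-hospitalization and that secondary endpoints are studied beyond it for this reason. A death, or a first infection, decompensation or bleed after an admission, enters its own Cox model. Repeat admissions may also appear in the descriptive multi-state model and, as serious adverse events, in the summaries by arm. Neither is a stated treatment comparison, and the multi-state model leaves out infections.

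Lastly, the article condenses a fuller protocol, and a definition of rate or a count analysis may stand there or in an analysis plan. That is fair, and the point does not rest on silence: it concerns a method the article does state, set against the objectives it states. The article mentions a pharmacoeconomic assessment but gives no method for it, so no argument is built on its data needs. Time-to-first analysis of secondary endpoints is a valid choice, and the proposal adds to it.

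**Conclusion.** The point holds in a limited form. Under the stated method, read as analogous to the primary analysis, repeat unplanned re-hospitalizations and repeat infections enter no comparison between the arms. The primary analysis is unaffected, because its objective is explicitly the first event.

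A reader might infer from the sample-size assumptions that about half of the expected events go unanalysed. That is too strong. The 53% applies to admissions only and needs nearly all of the composite hazard to be admissions and to recur unchanged. The plausible range is wide (about 11% to 70%), it rests on assumed death shares and later rates, and no figure exists for infections. What can be said is that a material share of admissions is likely to fall outside the stated comparison, of a size the document does not fix.

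**What to change.** Keep all time-to-first analyses as planned, and make two changes.

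1. State, for re-hospitalization and for infections, whether rate means the proportion of patients with an event or the number of events per patient-time.
2. Add a supportive secondary analysis: a rate ratio between arms for all unplanned re-hospitalizations, and one for all infections, to day 360. Use either the Lin-Wei-Yang-Ying marginal rate model with robust variance or a negative binomial model with a follow-up offset, adjusted for MELD stratum and centre. Name one of the two in advance. Report it alongside mortality, with a joint frailty model that treats death as a terminal event as sensitivity analysis.

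The cost is analysis-plan text and some extra programming. Table 4 already schedules endpoint assessment at every visit and telephone interview after baseline. The downside is interpretive: death ends the risk of further events, so an arm with more deaths can show fewer admissions, and the rate ratio must not be read without the mortality result.

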### Methods in analysis to handle protocol non-adherence and any statistical methods to handle missing data {20c}

In the primary analysis, dropout will be dealt with as independent right censoring. In case of substantial dropout, this assumption will be investigated in sensitivity analyses, e.g. shared random effects models. Missing data in baseline variables will be handled by multiple imputation.

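### Kaplan-Meier display of secondary endpoints that death can preclude overstates their absolute risk; the primary test and the hazard ratios are unaffected

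*Protocol article*

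**What the plan says.** Section {20a} of the protocol article tests the primary composite by Cox regression. For the individual components and the secondary endpoints, the analysis "will be performed analogously with the (cause-specific) Cox model". The next sentence fixes the display: "Time to event outcomes will be visualized by Kaplan-Meier curves stratified by treatment group". It makes no exception, and the article names no cumulative incidence estimator.

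The Objectives ({7}) list overall and liver-related death, "Time to and rate of unplanned re-hospitalization", infections, decompensation/ACLF and gastrointestinal bleeding. Under Outcomes ({12}), secondary endpoints continue to be followed after a first re-hospitalization.

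The one planned method that can represent competing events directly is in {20b}: the composite will also be described by "applying a multi-state model with states of unplanned re-hospitalization and death". On censoring, {20c} says "In the primary analysis, dropout will be dealt with as independent right censoring". That sentence concerns dropout, and the article does not say how deaths enter the curves for non-fatal endpoints.

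**The concern.** A patient who dies can no longer have a first infection, decompensation, bleed or re-hospitalization, and a patient who dies of a non-liver cause can no longer die of liver disease. The term cause-specific in {20a} recognises this. A Kaplan-Meier curve for such an endpoint does not: it removes the dead as if they could still have the event later. The quantity 1-KM then describes a hypothetical setting without competing death and lies above the proportion of patients who actually have the event.

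Deaths within 360 days are to be expected, since Table 1 does not exclude patients whose life expectancy is under one year because of cirrhosis. The sample size section also assumes lower mortality after withdrawal, so the overstatement would be larger in the control arm. A comparison of absolute risks read from the curves would then be shifted. This matters most for bleeding, because the abstract says that an increase in bleeding after withdrawal could support more liberal prescribing.

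**Working it through.** **Plan's own figures.** The plan gives no figure on this point. As a check of its inputs, the assumed 6-month risks of 50% and 65% give HR = ln(0.50)/ln(0.35) = 0.660, matching the stated 0.66. Schoenfeld's formula then gives 183 events and Freedman's 188, against the stated 184. Nothing below depends on the event count.

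**Method.** Take constant hazards over 12 months, with λe for the event and λd for competing death.

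- 1-KM = 1 − exp(−λe), so λe = −ln(1 − [1-KM]).
- λd = −ln(1 − D), where D is the 12-month competing death risk.
- Cumulative incidence = λe/(λe + λd) × (1 − exp(−(λe + λd))).

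The documents do not give D, so 10%, 20% and 30% are assumed.

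**Worked case.** For a 1-KM of 30% and D = 20%, λe = 0.3567 and λd = 0.2231, with sum 0.5798. The cumulative incidence is 0.3567/0.5798 × (1 − 0.70 × 0.80) = 0.615 × 0.44 = 27.1%, an excess of 2.9 points.

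**Range.** Cumulative incidence, with the excess of 1-KM in points in brackets:

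| 1-KM | D = 10% | D = 20% | D = 30% |
|---|---|---|---|
| 10% | 9.5% (0.5) | 9.0% (1.0) | 8.4% (1.6) |
| 30% | 28.6% (1.4) | 27.1% (2.9) | 25.5% (4.5) |
| 50% | 47.7% (2.3) | 45.4% (4.6) | 42.9% (7.1) |

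**Simulation.** With 238 patients per arm, a true 1-KM of 30%, D = 20% and a further 20% dropout, mean 1-KM over 500 runs was 30.0% and mean Aalen-Johansen 27.1%. 1-KM was the higher in all 500 runs.

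**Difference between arms.** Suppose both arms show the same 1-KM, with assumed 12-month death of 30% under continuation and 20% under withdrawal. At a 1-KM of 30% the actual risks are 25.5% and 27.1%, a difference of 1.6 points that the curves would not show. At a 1-KM of 10% they are 8.4% and 9.0%, a difference of 0.6 points.

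**First re-hospitalization.** Extrapolating the plan's 6-month composite risks at constant hazard gives 1 − 0.35² = 87.75% (control) and 1 − 0.50² = 75% (withdrawal) at 12 months. Let death make up an assumed share of first events:

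| Share of first events that are deaths | Control: 1-KM / cumulative incidence | Withdrawal: 1-KM / cumulative incidence |
|---|---|---|
| 5% | 86.4% / 83.4% | 73.2% / 71.3% |
| 10% | 84.9% / 79.0% | 71.3% / 67.5% |
| 20% | 81.4% / 70.2% | 67.0% / 60.0% |

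Only deaths before re-hospitalization compete here. The article's Discussion expects most deaths to come afterwards, so the upper rows are the more plausible ones.

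**The case against.** The strongest reply is that the sentence concerns display only. The planned effect measure is the hazard ratio, and a cause-specific Cox model that censors competing deaths is valid for what it estimates. This stands in full: neither the primary test nor any hazard ratio changes. A Kaplan-Meier curve can also serve as a visual companion to a cause-specific hazard, but the article does not label it that way, and readers commonly take such curves as risks.

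Second, the Objectives use time-to wording only for death and re-hospitalization; infection, decompensation and bleeding are called rates. That each will have a Kaplan-Meier curve, with deaths censored, is inferred from the Cox sentence and is not written out. It remains the natural reading, because {20a} sends the secondary endpoints to a Cox model and then prescribes one display for time-to-event outcomes.

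Third, the full protocol and the analysis plan are not shown. That would answer an omission. Here a method is named, and a document that follows it inherits the problem.

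Fourth, the multi-state model can give the correct probability for re-hospitalization. This stands as a partial answer for that endpoint. The model does not extend to infection, decompensation/ACLF, bleeding or liver-related death.

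Two stronger readings are tempting. A reader might infer that the pharmacoeconomic assessment would be wrong; the article mentions that assessment in one sentence and nowhere says that it uses these curves. A reader might also infer that every displayed risk is off by several points; the table shows that this fails for infrequent endpoints.

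**Conclusion.** The point holds as a correction to the display of secondary endpoints. The direction is certain: 1-KM with competing deaths censored cannot lie below the cumulative incidence, and it lies above once an event follows a competing death. The size rests on assumed mortality and constant hazards. For competing death of 10% to 30% at 12 months, it runs from half a point for an endpoint near 10% to about 7 points for one near 50%.

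For liver-related death only non-liver death competes. Table 1 excludes patients with a life expectancy under one year from extrahepatic disease, so the excess there is probably smaller than the table suggests. Kaplan-Meier is correct for the composite and for all-cause death. The documents do not support a claim that the trial's main conclusion, its hazard ratios or its sample size are affected.

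**What to change.** In {20a} and the analysis plan, restrict Kaplan-Meier curves to the composite endpoint and all-cause death. For first re-hospitalization, infection, decompensation/ACLF and gastrointestinal bleeding, show Aalen-Johansen cumulative incidence by arm with death as the competing event. For liver-related death, use non-liver death as the competing event. Give 95% confidence intervals at day 360, and place the curves beside the planned cause-specific hazard ratios for the event and for death.

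For re-hospitalization the multi-state model can supply the curve, provided it reports the probability of ever having been re-hospitalized and not of being alive in that state.

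The cost is a change of wording and standard software. No additional data, patients or tests are needed.

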### Interim analyses {21b}

After half of the required events, an interim analysis is planned with the opportunity to stop for futility if the p-value of the treatment group is > 0.5. Since this interim analysis does not inflate the type-one error α correction for multiplicity is not necessary.

### Methods for additional analysis (e.g. subgroup analyses) {20b}

The composite primary endpoint will additionally be analysed descriptively by applying a multi-state model with states of unplanned re-hospitalization and death. Both analyses of the composite primary endpoint will be repeated in the per-protocol (PP) set. Analyses of the primary and secondary endpoint in the following subgroups are planned: According to the Child-Pugh stage; according to the aetiology of cirrhosis; untreated or treated aetiology of cirrhosis (e.g. treated vs. untreated viral hepatitis); patients with a history of TIPS implantation. Further subgroups may be defined in ad-hoc analyses.

### Methods in analysis to handle protocol non-adherence and any statistical methods to handle missing data {20c}

In the primary analysis, dropout will be dealt with as independent right censoring. In case of substantial dropout, this assumption will be investigated in sensitivity analyses, e.g. shared random effects models. Missing data in baseline variables will be handled by multiple imputation.

